## Abstract

**Background:**

Declining levels of physical fitness in children are linked to an increased risk of developing poor physical and mental health. Physical activity programs for children that involve regular high intensity physical activity, along with muscle and bone strengthening activities, have been identified by the World Health Organisation as a key strategy to reduce the escalating burden of ill health caused by non-communicable diseases. This paper reports the rationale and methods for a school-based intervention designed to improve physical fitness and physical activity levels of Grades 5 and 6 primary school children.

**Methods/Design:**

Fit-4-Fun is an 8-week multi-component school-based health-related fitness education intervention and will be evaluated using a group randomized controlled trial. Primary schools from the Hunter Region in NSW, Australia, will be invited to participate in the program in 2011 with a target sample size of 128 primary schools children (age 10-13). The Fit-4-Fun program is theoretically grounded and will be implemented applying the Health Promoting Schools framework. Students will participate in weekly curriculum-based health and physical education lessons, daily break-time physical activities during recess and lunch, and will complete an 8-week (3 × per week) home activity program with their parents and/or family members. A battery of six health-related fitness assessments, four days of pedometery-assessed physical activity and a questionnaire, will be administered at baseline, immediate post-intervention (2-months) and at 6-months (from baseline) to determine intervention effects. Details of the methodological aspects of recruitment, inclusion criteria, randomization, intervention program, assessments, process evaluation and statistical analyses are described.

**Discussion:**

The Fit-4-Fun program is an innovative school-based intervention targeting fitness improvements in primary school children. The program will involve a range of evidence-based behaviour change strategies to promote and support physical activity of adequate intensity, duration and type, needed to improve health-related fitness.

**Trial Registration No:**

Australia and New Zealand Clinical Trials Register (ANZCTR): ACTRN12611000976987

## Background

The fitness levels of children and adolescence are in decline [1-3]. This is an alarming trend given that high levels of physical fitness in this age group are associated with improved physical and mental health both in the short -and long-term [4,5]. Recent studies have shown that children who display high levels of physical fitness, especially health-related fitness (HRF) [6], have a decreased risk of developing cardiovascular disease and other chronic illnesses (such as obesity, Type 2 diabetes mellitus, osteoporosis and some cancers) [7], are less likely to suffer from anxiety and depression [8], and more likely to perform better academically [9].

In response to the declining physical activity (PA) and physical fitness (PF) levels of children, and the corresponding increase in non-communicable diseases (NCD), the World Health Organization (WHO) published the *Global Recommendations on Physical Activity and Health *[10]. These recommendations address the link between the frequency, duration, intensity, type and total amount of physical activity needed for preventing NCD [10]. The WHO recommendations now outline that children aged 6-17 years should participate in at least 60 min of moderate-to-vigorous PA every day, and to perform vigorous PA (high intensity), muscle-strengthening PAs and bone-strengthening PAs, on at least three days per week [10]. As such, studies investigating and targeting children's health may also benefit from a redirected focus on regular vigorous intensity PA and improvements in HRF to improve overall health.

A recent review confirms that there is great public health potential for school-based interventions to improve the PA and PF levels of young people [11]. The school, via the curriculum, school ethos and community, is an ideal avenue for accessing and educating young people about the importance of PA, the value of achieving and/or maintaining HRF standards and for building the skills necessary for long-term behaviour change [12]. There are numerous opportunities in the school setting for the promotion of PA, including health and physical education (HPE), active transportation, active breaks, sport etc. While HPE is widely acknowledged the cornerstone of a schools' physical activity program, studies have questioned the quality and quantity of HPE lessons delivered in primary schools [13-15].

Recent studies have demonstrated positive results in improving HRF, especially cardio-respiratory fitness, via school- based interventions [11]. However, many have failed to address the multiple components that influence behaviour in the school setting, make reference to credible learning theories or curriculum direction in intervention designs, or specifically target improvements in all of the HRF components [16]. In addition, few studies have designed and tested multi-component programs to extend learning into the school playground and the home - potentially limiting the impact that the program has on health outcomes and behaviour change [16].

The Fit-4-Fun program is an innovative and engaging school-based fitness education program. It encompasses all of the components of a Health Promoting School [17], extends learning beyond the classroom and provides professionally designed curriculum resources for primary school teachers This study builds upon the Fit-4-Fun pilot study (conducted in 2010) and will provide further evidence to support the effectiveness of the Fit4Fun intervention for improving the HRF and PA levels of children, along with their attitudes towards physical fitness. This paper provides the rationale and study protocol of the Fit-4-Fun program.

## Methods/Design

### Study design

Fit-4-Fun is an 8-week multi-component school-based HRF education intervention and will be evaluated using a group randomized controlled trial (RCT) with 6-month follow-up. Ethics approval for the study was obtained from the University of Newcastle, NSW, Australia and the Newcastle-Maitland Catholic Schools Office, and is registered with the Australian and New Zealand Clinical Trials Registry (ACTRN12611000976987).

Following the initial recruitment process, all eligible participants will complete baseline assessments and follow-up measures will be conducted immediate post-intervention and at 6-months. The design, conduct and reporting of the Fit-4-Fun intervention will adhere to the Consolidation Standards of Reporting Trials (CONSORT) guidelines [18]. School Principals, teachers, parents and study participants will provide written informed consent.

### Recruitment & study participants

Primary schools from the Hunter Region in NSW, Australia, will be invited to participate in the Fit-4-Fun program in 2011. Initially, school Principals will be contacted via email and then a face-to-face meeting will be arranged. Written consent will be sought from both the Principal and the classroom teachers of each school before participants from Stage 3 classes (years 5 and 6) are recruited. All students are eligible to participate in the program if they return a signed informed consent letter from their parent(s) with child assent, and do not currently have a medical condition or physical injury preventing testing or training. Figure 1 depicts the flow of participants through the trial.

**Figure 1 F1:**
[figure not shown]
**Flow of participants through the Fit-4-Fun**.

### Sample Size Calculation

A battery of fitness assessments will be conducted to determine the HRF levels of participants. The primary outcome variable in this study is cardio-respiratory fitness. A power calculation was conducted to determine the sample size necessary to detect changes in cardio-respiratory fitness (VO2max). Based on a previous study by Kolle et.al (2009), an increase of 6 mL/kg/min was regarded as clinically important and achievable in children [19]. Using an alpha of 0.05 and power of 80%, a sample size of 128 will be needed to detect a 6 mL/kg/min difference between groups. To account for the clustered nature of the data and participant drop-out, we will aim to recruit 200 participants from four schools.

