### Blinding & Randomization

Participants and research assistants will be blinded to treatment conditions during baseline assessments. Randomization by school will be performed at the completion of baseline assessments and the four participating schools will be randomly assigned to the Fit-4-Fun intervention (2 schools) or a 9-month wait-list control group (2 schools). A randomization envelope will be prepared by a member of the research team and an independent third party will blindly allocate the four schools into one of the two treatment conditions.

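### The claimed 80% power for 6 mL/kg/min is not delivered: 200 children in four schools covers an ICC of only about 0.01, and the comparison of arms has 2 degrees of freedom

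*Protocol article*

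**What the plan says.** The protocol article, under Sample Size Calculation, names cardio-respiratory fitness as the primary outcome and a 6 mL/kg/min difference between groups as the target. It states: "Using an alpha of 0.05 and power of 80%, a sample size of 128 will be needed". It then moves to the recruitment figure: "To account for the clustered nature of the data and participant drop-out, we will aim to recruit 200 participants from four schools". Under Blinding & Randomization, "the four participating schools will be randomly assigned to the Fit-4-Fun intervention (2 schools) or a 9-month wait-list control group (2 schools").

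The section gives no SD, ICC or drop-out rate. Statistical Methods says the linear mixed models will adjust for clustering and names no degrees-of-freedom method. The Abstract still gives 128, not 200, as the target sample.

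**The concern.** The paragraph asserts that raising 128 to 200 deals with clustering and drop-out, so that the 80% power stands. That assertion can be tested with the article's own figures, and two things look wrong.

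- **The inflation is small.** With about 50 children in each school, even a small ICC produces a large design effect, and the same 72 extra children must also cover drop-out.
- **There are only four randomised units.** An inflation factor corrects the variance but not the critical value, and with two schools per arm the critical value more than doubles.

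This is the primary comparison. The Discussion expects the trial to settle whether the program is effective enough for wider use. If the trial can rarely detect its own target difference, a non-significant result published beside an 80% power claim invites the wrong reading.

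**Working it through.** **Inputs from the article.** Alpha 0.05 (taken as two-sided; sidedness is not stated), power 80%, difference 6 mL/kg/min, base sample 128, recruitment 200, four schools, two per arm.

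**Assumed, because not given.** ICC from 0 to 0.10; drop-out 0%, 10% and 20%; equal schools of m = 50 when nobody drops out.

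**1. Reproducing 128.** A two-sample t-test at d = 0.5, two-sided 0.05, 80% power needs 63.8, so 64 per arm and 128 in total (power 80.1%). Hence the implied SD is 6/0.5 = 12 mL/kg/min. Other SDs give other totals: SD 6 gives 34, SD 8 gives 58, SD 10 gives 90. So 128 is a child-level calculation with no clustering in it.

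**2. The ICC that 200 can absorb.** The number analysed, n = 200(1 − drop-out), divided by the design effect 1 + (n/4 − 1)·ICC, must be at least 128. The limit is therefore

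ICC = (n/128 − 1)/(n/4 − 1)

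- No drop-out: 0.5625/49 = 0.0115
- 10% drop-out (n = 180): 0.40625/44 = 0.0092
- 20% drop-out (n = 160): 0.25/39 = 0.0064
- 36% drop-out (n = 128): 0

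This step uses no SD. For comparison, at 50 per school an ICC of 0.02 needs 128 × 1.98 = 253 children and 0.05 needs 128 × 3.45 = 442. With only four schools the effective sample cannot exceed 4/ICC, so once the ICC reaches 4/128 = 0.031 no number of children per school yields 128.

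**3. Power with the actual randomised units.** With two schools per arm,

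Var(difference) = SD²[ICC + (1 − ICC)/m]

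The noncentrality is 6/√Var, and the school-level df are 4 − 2 = 2. For example, with SD 12, m = 50 and ICC 0.01: Var = 144 × (0.01 + 0.0198) = 4.29, SE = 2.07, noncentrality = 2.90. With 2 df, 80% power needs a noncentrality of 5.65 (against 2.80 for the normal approximation), so the detectable difference is 5.65 × SE.

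Results for SD 12, 200 children, no drop-out:

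| ICC | Power, normal approx. | Power, 2 df | Detectable at 80%, 2 df (mL/kg/min) |
|---|---|---|---|
| 0 | 94% | 48% | 9.6 |
| 0.01 | 82.5% | 37% | 11.7 |
| 0.02 | 71% | 30% | 13.5 |
| 0.05 | 48% | 20% | 17.8 |
| 0.10 | 31% | 14% | 23.3 |

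Simulating school means for two against two schools gave 48.4% at ICC 0 and 36.9% at ICC 0.01. With 20% drop-out the 2-df power falls to 42% and 33% at those ICCs.

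**4. Sensitivity to the SD (2 df, 200 children, no drop-out).**

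| SD | ICC 0.01 | ICC 0.05 | Total the t-test would need |
|---|---|---|---|
| 6 | 81.5% | 53% | 34 |
| 8 | 62% | 36% | 58 |
| 10 | 47% | 26% | 90 |
| 12 | 37% | 20% | 128 |

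The largest SD at which 80% is reached with 2 df is 7.5 at ICC 0, 6.1 at 0.01, 5.3 at 0.02 and 4.0 at 0.05.

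**The case against.** The strongest reply is that SD 12 is my inference, not the article's figure. If the true SD is much smaller, 200 children may be less inadequate than the headline numbers suggest: at SD 6 and ICC 0.01 the 2-df power is 81.5% with no drop-out. That is correct, but it does not rescue the paragraph. At SD 6 the requirement would have been 34 children, so the stated 128 would be wrong instead.

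A second reply is that fitness is measured at baseline and the mixed model may use it. If, as an assumption, baseline and follow-up correlate at 0.7 to 0.8, a raw SD of 12 becomes a residual SD of 12√(1 − 0.49) = 8.6 to 12√(1 − 0.64) = 7.2. At ICC 0.01, the larger of these exceeds the 6.1 limit, and so does the smaller. Only at ICC 0 does 7.2 fall under the limit (7.5). Adjustment may also shrink the between-school component, so some gain is possible. The article claims none, and if 128 was meant for the adjusted analysis, the 12 is already the residual SD.

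Third, the analysis adjusts for clustering, and a model on child-level df would show higher nominal power. Adjustment does not restore power, and with two schools per arm child-level df would not protect the type I error if the ICC is above 0.

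Finally, a condensed article may leave the SD, ICC and drop-out to a fuller document. That is fair, and their absence alone is not the fault. The fault is the printed claim that 200 children in four schools suffices for 80% power. Nothing here says what the true ICC is.

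**Conclusion.** The concern holds. The ICC ceiling of about 0.01 follows from 128, 200 and four schools alone: 0.0115 at best, and lower with any drop-out. The 2 df follow from two schools per arm. At the standardised difference that 128 implies (about 0.5), power is 48% with no clustering and no drop-out, 37% at ICC 0.01 and 20% at ICC 0.05. The detectable difference at ICC 0.01 to 0.05 is 11.7 to 17.8 mL/kg/min, two to three times the target.

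The power figures rest on SD 12, equal schools of 50, a two-sided test, no credit for baseline adjustment and inference on school-level df. Relaxing the SD enough to reach 80% contradicts the stated 128, so the paragraph cannot be right as it stands. It must be corrected.

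**What to change.** Rewrite the Sample Size Calculation paragraph. State the investigators' own SD, ICC and drop-out, say whether the SD is raw or baseline-adjusted, and give the power or the detectable difference for two schools per arm with 2 df. Withdraw the 80% claim and describe the trial as estimating the effect with a confidence interval. As an example of form only, using the SD implied by 128: with 200 children in four schools, SD 12, ICC 0.01 to 0.05 and no drop-out, power for 6 mL/kg/min is about 37% to 20%. Bring the Abstract's target of 128 into line with the 200 in the Methods.

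The cost is one reworded paragraph and one figure in the Abstract, with a less favourable stated power. No added participants are required. Randomising more schools would be the real remedy for the power itself, but this correction does not depend on it.

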### Blinding & Randomization

Participants and research assistants will be blinded to treatment conditions during baseline assessments. Randomization by school will be performed at the completion of baseline assessments and the four participating schools will be randomly assigned to the Fit-4-Fun intervention (2 schools) or a 9-month wait-list control group (2 schools). A randomization envelope will be prepared by a member of the research team and an independent third party will blindly allocate the four schools into one of the two treatment conditions.

### Training

Research assistants will conduct and record all physiological assessments, and will administer the student questionnaire. All research assistants will complete an identical training session prior to assessments to maintain consistency and where possible the same assessors will be used for all assessments.

### Treatments

#### a) Intervention

##### Theoretical framework

The Fit-4-Fun Program is grounded in Bandura's Social Cognitive Theory and Harter's Competence Motivation Theory and aims to provide children with the knowledge and skills necessary for short- and long-term behaviour change [20,21]. The program also aims to promote the development and maintenance of positive PA behaviours and attitudes among participants, by targeting possible mediators of behaviour change (e.g. social support, self-efficacy, supportive environment, enjoyment) [21,22]. An overview of the Fit-4-Fun program content and alignment with theoretical constructs is reported in Table 1.

**Table 1 T1:** 'Fit-4-Fun' program content and alignment with theoretical constructs

Wk	Session focus	Session overview	Behaviour change strategies	SCT/CMT construct
**1**	Health-related fitness (theory)	• Programme rational • Defining PA & PF • HRF & SRF • PA guidelines • Analysing current PA & PF behaviours • Overview of 'Home Activity Programme'	• Provide information about PA & PF behaviours/link to health • Develop self-monitoring skills (weekly PA timetable, talk test) • Provide social support and encouragement (to meet PA guidelines) • Develop goal setting skills (HW task)	• Outcome expectations • Social support (home & school) • Self-efficacy • Intentions • Motivation

**2**	Cardio-respiratory fitness (CRF) (theory)	• Provide information on CRF • Role of heart & lungs during PA • Linking heart rate (HR) to PA intensity (lab) • Linking CRF & health	• Provide information about CRF & the role of the heart & lungs during PA • Develop skills in self-monitoring (using heart rate) • Predicting consequences of actions • Making recommendations relating to PA and CF	• Outcome expectations • Self-efficacy • Social support • Motivation

**3**	Improving cardio-respiratory fitness (practical)	• Revise CRF & measuring intensity using HR • Participate in a practical PE lesson with a gross motor warm-up activity, dynamic stretches, skill development activities, modified games and cool-down • HR is monitored throughout the lesson • Discussion about the type of PA and heart rate (high intensity/vigorous)	• Provide opportunity to participate in enjoyable physical activities in a supportive environment • Maximal participation is provided for and encouraged • Positive feedback is provided throughout the session • Students are to reflect on their performance and re-assess current PA behaviours	• Outcome expectations • Social support • Self-efficacy • Motivation

**4**	Muscular Fitness (MF) (theory)	• Define MF • Muscular strength Vs Muscular endurance • Activities that require MF • Measuring MF (lab) • Linking MF & health • Improving MF	• Provide information on MF • Link current PA behaviour to MF • Develop goal setting skills/set targets to achieve • Self-monitoring skills (PF tests) • Participation in non-threatening practical assessments (enjoyment)	• Outcome expectations • Social support • Self-efficacy • Intentions • Motivation

**5**	Improving muscular fitness (practical)	• Revise MF & measuring MF • Participate in a practical PE lesson with a gross motor warm-up activity, dynamic stretches, MF circuit and cool-down • HR is monitored throughout the lesson • Discussion about the type of PA and MF (resistance)	• Provide opportunity to participate in enjoyable physical activities in a supportive environment • Maximal participation is provided for and encouraged • Positive feedback is provided throughout the session • Students are to reflect on their performance and re-assess current PA behaviours	• Outcome expectations • Social support • Self-efficacy • Motivation

**6**	Flexibility (theory)	• Define flexibility • Activities that require MF • Benefits of being flexible • Types of stretching • Improving flexibility (lab) • Linking MF & health • Improving MF • Predicting outcomes from changed MF behaviours • Goal setting task • Link flexibility to lifestyle behaviours	• Provide information on flexibility • Link current PA behaviour to flexibility • Develop goal setting skills/set targets to achieve • Self-monitoring skills (PF tests) • Participation in non-threatening practical assessments (enjoyment)	• Outcome expectations • Social support • Self-efficacy • Intentions • Motivation

**7**	Improving flexibility (practical)	• Revise flexibility and measuring flexibility • Participate in a practical PE lesson with a gross motor warm-up activity, dynamic stretches, fun stretching routines and cool-down • HR is monitored throughout the lesson • Discussion about the type of PA and improved flexibility	• Provide opportunity to participate in enjoyable physical activities in a supportive environment • Maximal participation is provided for and encouraged • Positive feedback is provided throughout the session • Students are to reflect on their performance and re-assess current PA behaviours • Link to lifelong behaviours	• Outcome expectations • Social support • Self-efficacy • Motivation

**8**	Improving health-related fitness through games (practical)	• Revise HRF components • Revise improving HRF • Participate in a student-centred practical PE lesson where students adapt fun games to incorporate HRF • HR is monitored throughout the lesson • Discussion about the type of PA and improved HRF • Summary of health benefits with improved HRF • Evaluation of 'Fit-4-Fun'	• Provide opportunity to participate in enjoyable physical activities in a supportive environment • Maximal participation is provided for and encouraged • Positive feedback is provided throughout the session • Students learn skills in adapting PA to improve HRF • Students are to reflect on their performance and re-assess current PA behaviours • Link to lifelong behaviours	• Outcome expectations • Self-efficacy • Social Support • Motivation

**1-8**	'Fit-4-Fun' Home Activities	• Participation in an 8 week home activity programme • 3 weekdays: MF, flexibility, CRF activities • 1 weekday: fitness assessments • Weekends: family activities & CRF assessment • Weeks 1, 5, 8: Goal setting tasks • Problem Solving Task (assessment)	• Students participate in a range of fun activities with their parents/siblings • Family provide social support throughout the programme • Students develop skills in self-monitoring and self-motivating • Students develop skills in goal setting & time management • Students develop skills in assessing & planning to improve the physical environment	• Outcome expectations • Self-efficacy • Social Support • Motivation

Abbreviations: SCT- Social Cognitive Theory; CMT - Competence Motivation Theory; HRF - Health-Related Fitness; HR - Heart rate;

CRF - Cardio-respiratory fitness; MF - Muscular fitness; PA- Physical activity

The Fit-4-Fun Program includes three major components that are based on the HPS Framework [17]:

